## **16. Access to Source Documents**

Source documents in this study include:

1. Records of participant consent and data disclosure.
2. Medical records, laboratory data, imaging results, registration data, and other records serving as the basis for case report forms.

The coordinating investigator, site investigators, and institutions shall make all clinical research-related records and source documents available for direct inspection by monitors, the CRB, or regulatory authorities as required.

## 17. Periodic Reporting

The coordinating investigator will submit an annual report on the study's implementation status to both the site administrators and the Certified Review Board (CRB), within two months after each one-year period following the public registration date on the Japan Registry of Clinical Trials (JRCT).

The report will use Unified Form No. 5 and Annex Form No. 3.

### The annual report shall include:

1. Number of participants enrolled.
2. Occurrence and outcomes of study-related diseases or adverse events.
3. Noncompliance with regulations or protocol and the corresponding corrective actions.
4. Evaluation of study safety and scientific validity.
5. Details of involvement by any pharmaceutical or medical device manufacturers.

Within **one month** after receiving CRB review comments, the coordinating investigator will submit the following to the MHLW using Annex Form No. 3:

1. Name of the CRB listed in the implementation plan.
2. CRB judgment regarding continuation or suspension of the study.
3. Number of participants enrolled.

The coordinating investigator will share the contents of periodic reports with all site investigators.

Each site investigator shall promptly report the shared information to the administrator of their institution.

## 18. Funding Source, Conflict of Interest, and Financial Relationships

This study is supported by the following funding sources:

- Operational grants of the Department of Periodontology, Okayama University Hospital.
- Clinical Research Promotion Fund of Okayama University Hospital.
- Japan Agency for Medical Research and Development (AMED) through the "Project for Practical Application of Innovative Cancer Medical Care."
- Provision of the investigational device by Sun Medical Co., Ltd.

The coordinating investigator will disclose any conflicts of interest (COI) in accordance with the "Guidance on COI Management under the Clinical Trials Act" and obtain CRB approval.

Any updates or changes in institutional or personal COI will be reviewed and reported in each periodic report to the CRB.

Participants will not incur any additional costs for the use of the investigational device; all expenses remain within the scope of standard clinical care.

## **19. Public Disclosure of Study Information**

This study is registered in the Japan Registry of Clinical Trials (jRCT). Results obtained from this study will be published in the jRCT registry, presented at academic conferences such as the Japanese Breast Cancer Society and the Japanese Society for Supportive Care in Cancer, and submitted as a manuscript to a peer-reviewed journal specializing in oncology supportive care.

## **20. Participant Inquiries and Complaints**

The coordinating investigator and all site investigators will respond promptly and appropriately to any inquiries, consultations, or complaints from participants or their representatives.

Inquiry Contacts:

**25. Management of Adverse Events, Device Malfunctions, and Related Procedures**

**(1) Definition of Adverse Events and Device Malfunctions**

In this specified clinical trial conducted under the Japanese Clinical Trials Act, “adverse events” refer to any illness, disability, death, infection, or device malfunction that is suspected to be causally related to the conduct of the study.

In this study, the principal and sub-investigators will document all adverse events observed from the start of the comparative period until the end of the continuous treatment period.

Events that occur before device removal due to chemotherapy delay will also be included as evaluation targets.

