## **4. Study Methods**

### **(1) Study Type and Design**

This is a multicenter, prospective, open-label, randomized, parallel-group comparative study.

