#### **(4) Confirmation of Adverse Events, Illnesses, and Device Malfunctions**

All adverse events, illnesses, and device malfunctions will be recorded in the electronic Case Report Form (eCRF), including details, onset/resolution dates, severity, treatment, outcome, seriousness assessment, and causal relationship to device use.

Follow-up investigations will be performed as needed.

Events occurring prior to device removal due to chemotherapy delay will also be included in safety evaluations.

Symptoms or disease progression attributable to the primary malignancy or to anticancer therapy itself will not be considered adverse events in this study.

For participants allocated to the control group during the comparative period, assessment of device-related malfunctions or causality is not applicable.

413 Schedule

| Period                                     | Screening period
a) / Enrollment     | Comparative period                   |                                              |                                    | Continuous period:
When chemotherapy is administered after the comparative period, existing therapy is combined with the filling of the investigational device irrespective of group assignment. |
|--------------------------------------------|-----------------------------------------|--------------------------------------|----------------------------------------------|------------------------------------|-----------------------------------------------------------------------------------------------------------------------------------------------------------------------------------------------------|
| Assessment date                            | —                                       | Day of study procedure
(Day 1) g) | End of comparative period (Day 14 / 21 / 28) | (At discontinuation)               | End of continuous period (Day 14 / 21 / 28)                                                                                                                                                         |
| Allowable range                            | Day -56 to Day -1
(before procedure) | Assessment date (Day 0)              | Assessment window: Day -7 to +7              | Discontinuation date (Day 0 to +1) | Assessment window: Day -7 to +7                                                                                                                                                                     |

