| Administration of G-CSF (yes/no)           | ●                                       | ●                                    | ●                                            | ●                                  | ●                                                                                                                                                                                                   |
| Blood tests (hematology and biochemistry)  | ● i)                         |                                      | ●                                            | ●                                  | ●                                                                                                                                                                                                   |

- c) Assessments marked accordingly must be performed prior to the investigational procedure.
- d) If the investigational device dislodges before the end of any treatment period, the date and time of dislodgement must be recorded in the patient diary.
- e) For participants assigned to the control group during the comparative period, the specified assessments and examinations for the comparative period are not required.
- f) Symptoms or disease progression related to the underlying breast cancer, as well as events directly caused by chemotherapy, are not regarded as adverse events in this study. Events occurring before device removal due to chemotherapy delay will still be evaluated. For participants in the control group during the comparative period, assessment of causal relationship between adverse events and device filling is not applicable.
- g) The day on which participants visit the site for device application prior to chemotherapy shall be defined as Day 1 (start of the comparative period). Chemotherapy should be administered within 0–3 days after device application, and the actual chemotherapy date must be recorded. If chemotherapy is postponed, the device should be temporarily removed, and the device application date reset in accordance with the rescheduled chemotherapy.
- h) Evaluate whether natural dislodgement, brushing-related dislodgement, meal-related dislodgement, or self-removal by the participant occurred. If such events occur before temporary device removal due to chemotherapy delay, they must also be included in the evaluation.

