### **(4) Protocol Amendments**

Safety-related information will be continuously reviewed, and the protocol and consent documents will be amended if necessary.

All amendments must be approved in advance by the Certified Review Board (CRB).

Amendments will be submitted to MHLW as follows:

739       • **Substantial amendment:**

- 740           1. *Notification of change in implementation plan* (Form No. 2, Ministerial Ordinance)  
741           2. *Revised implementation plan*

742       • **Minor amendment:**

- 743           1. *Notification of minor change in implementation plan* (Form No. 3)  
744           2. *Revised implementation plan*

745 For minor administrative changes (e.g., investigator contact details, institutional name updates),  
746 notification to the CRB will be made within 10 days, accompanied by submission of Form No. 3 to  
747 MHLW.  
748

749 **(5) Criteria for Discontinuation**

750 When continuation is deemed impossible, the investigator shall discontinue the participant's  
751 involvement, explain the reason if appropriate, and ensure that post-discontinuation medical care is  
752 provided without disadvantage.

753 **Reasons for discontinuation include:**

- 754       1. Participant requests to withdraw. (The reason will be confirmed if possible, but not required.)  
755       2. Worsening of primary disease, chemotherapy-related symptoms, or requirement for  
756       disallowed concomitant therapy.  
757       3. Occurrence of adverse events making continuation difficult.  
758       4. Noncompliance with the protocol.  
759       5. Ineligibility determined upon further observation after registration.  
760       6. Any other reason judged by the investigator to make continuation inappropriate.

761 **In case of treatment discontinuation:**

762 If continuation of the investigational treatment is deemed impossible for the above reasons, treatment  
763 will be discontinued with an appropriate explanation to the participant.

764 Participants who have received the investigational device will continue safety follow-up observations  
765 even after discontinuation.  
766

767 **15. Storage and Disposal of Study Records and Data (Including Retention Period)**

768 The principal investigator shall prepare and maintain records regarding:

- 769       1. Identification of each study participant.

2. Clinical care and testing performed for participants.
3. Details related to study participation.

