**(3) Severity Grading**

Severity of adverse events will be determined using the Common Terminology Criteria for Adverse Events (CTCAE) v5.0, Japanese JCOG version.

For events not listed in CTCAE, the following classification will apply:

| Grade              | Description                                                                                 |
|--------------------|---------------------------------------------------------------------------------------------|
| Grade 1 (Mild)     | Asymptomatic or mild symptoms; clinical or laboratory findings only; no treatment required. |
| Grade 2 (Moderate) | Minimal, local, or noninvasive intervention indicated; limitation of instrumental ADL.      |

| Grade                      | Description                                                                                                                 |
|-----------------------------------|------------------------------------------------------------------------------------------------------------------------------------|
| Grade 3 (Severe)           | Medically significant but not immediately life-threatening; hospitalization or prolongation required; limitation of self-care ADL. |
| Grade 4 (Life-threatening) | Urgent intervention indicated.                                                                                                     |
| Grade 5 (Fatal)            | Death related to the event.                                                                                                        |

908

909 **(4) Assessment of Frequency**

910 For recurrent or intermittent events that appear to resolve and recur, the investigator may consider  
911 them as a single event if judged clinically continuous from onset to final resolution.

912

913 **(5) Causality Assessment**

914 The investigator will evaluate the relationship of each adverse event or malfunction to both the  
915 investigational device (novel oral mucosal protectant) and study procedures, taking into account:

- 916 • Temporal relationship to device use
- 917 • Underlying disease course
- 918 • Concomitant medications or therapies
- 919 • Procedural deviations or accidents

920 Causality will be classified as:

- 921 1. **Related** (reasonable possibility, cannot be ruled out), or
- 922 2. **Not related** (no reasonable causal relationship).

923

924 **(6) Outcome Classification**

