925 All adverse events will be followed until resolution or stabilization, or until further follow-up is  
926 deemed unnecessary by the investigator.

927 Outcomes will be categorized as follows:

- 928 1. Recovered
- 929 2. Improved
- 930 3. Not recovered (unchanged or worsened)
- 931 4. Recovered with sequelae

- 932        5. Death  
933        6. Unknown  
934

935    **(7) Expectedness and Anticipated Events**

936    Expectedness will be assessed based on the product's approved labeling information or prior clinical  
937    experience.

938    If the nature, severity, or frequency is inconsistent with known data, it will be considered unexpected.

939    Possible adverse events and anticipated frequencies include:

940    **Incidence  $\leq$  1%**

- 941        1. Abdominal pain, diarrhea  
942        2. Taste disturbance

943    **Incidence  $\leq$  0.1%**

- 944        3. Allergic reaction to mucosal protectant components  
945        4. Microbial substitution phenomena  
946        5. Pulpal disorders

947    **Possible Device Malfunctions**

- 948        6. Discomfort during device wear  
949        7. Detachment from filling site  
950        8. Accidental swallowing due to intraoral detachment  
951        9. Aspiration due to intraoral detachment

952

953    **(8) Responsibilities and Reporting of Serious Adverse Events**

- 954        1. The principal/sub-investigator must take all necessary actions (explanation to participant,  
955        treatment, etc.) immediately upon recognizing an SAE.
- 956        2. The principal investigator must promptly report the event to the institutional administrator  
957        and the coordinating investigator.
- 958        3. The coordinating investigator will report to the Certified Review Board (CRB) using Unified  
959        Report Form No. 9 and share relevant information with investigators at other sites.
- 960        Site investigators must promptly notify their institutional administrators upon receiving such  
961        information.

4. The coordinating investigator must also report any event meeting MHLW requirements using Supplementary Form No. 2-2 (for medical devices) to the Minister of Health, Labour and Welfare, following the timelines below.

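### The adverse event definition and the chemotherapy exclusion let open-label attribution remove or distort the symptom-type events anticipated from the device

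*Protocol*

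**What the plan says.** **Definition.** Protocol Section 25(1), which refers to the Clinical Trials Act, defines adverse events as "any illness, disability, death, infection, or device malfunction that is suspected to be causally related to the conduct of the study". The duty in the same section to document all adverse events, from the start of the comparative period to the end of the continuous period, uses that term.

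**Recording.** Section 5(4) says that all adverse events, illnesses and device malfunctions go into the eCRF, with the causal relationship to device use as one recorded item. Section 25(5) sorts events into related, which includes cases where causality cannot be excluded, and not related, glossed as "no reasonable causal relationship".

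**Exclusion.** Section 5(4) adds: "Symptoms or disease progression attributable to the primary malignancy or to anticancer therapy itself will not be considered adverse events in this study". Note f to the schedule repeats this for events of the underlying cancer, "as well as events directly caused by chemotherapy, are not regarded as adverse events in this study".

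**Setting.** Section 4(1): "This is a multicenter, prospective, open-label, randomized, parallel-group comparative study". Inclusion criterion 1 requires scheduled chemotherapy. Chemotherapy starts within three days after device placement (Section 4(4), Intervention Procedures). For controls in the comparative period, note f says that "assessment of causal relationship between adverse events and device filling is not applicable".

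**Anticipated events.** Section 25(7) lists "Abdominal pain, diarrhea" and taste disturbance at an incidence of at most 1%. Allergic reaction, microbial substitution and pulpal disorders are listed at at most 0.1%. Discomfort, detachment, swallowing and aspiration are listed as malfunctions.

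**The concern.** A safety record is easiest to interpret when events are collected first and attributed afterwards. Here two attribution judgements come before collection. Section 25(1) asks whether the event is suspected to be related to the study. Section 5(4) and note f ask whether it belongs to the cancer or the chemotherapy. An event that fails either test is, by the protocol's terms, not an adverse event, so the instruction to record all adverse events does not recover it.

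The person who judges knows the arm. The symptoms anticipated from the device are non-specific, and every participant also has chemotherapy as a candidate cause. Attribution could hide a device effect, if such symptoms are put down to chemotherapy. It could also create a false one, if they are kept as study-related more readily when a device is in place.

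At stake is the comparison of these symptoms in the comparative period. In the continuous period participants of both groups receive the device, so what is not recorded earlier cannot be recovered from a randomised contrast later.

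**Working it through.** **1. The passages side by side**

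| Place | Rule | Fit with the others |
|---|---|---|
| 25(1) | Suspected relation to study conduct is part of the definition | Narrow |
| 5(4), first part | All adverse events recorded; causality is a data item | Implies collection before attribution |
| 25(5) | Each event is then classed as related or not related | Little purpose for the second class if suspicion is required for entry |
| 5(4), later part; note f | Cancer- and chemotherapy-attributed events are not adverse events | A second filter, which remains even if 25(1) is read broadly |

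The thresholds in 25(5) and 5(4) can also collide. Diarrhea shortly after device placement and chemotherapy, which are 0 to 3 days apart, may be an event for which device causality cannot be excluded (hence related). It may equally be an event attributable to anticancer therapy (hence not an adverse event). No text says which rule prevails.

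**2. The plan's own sample size**

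Inputs (Section 7): 50% v 25%, two-sided 5%, 90% power, Pearson's chi-square.

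n = [1.960 × √(2 × 0.375 × 0.625) + 1.282 × √(0.25 + 0.1875)]² / 0.25² = 76.7, rounded up to 77 per group. This agrees with the protocol (power at 77 is 90.1%). The point does not depend on it, but 77 is the denominator used below.

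**3. Expected events at the protocol's anticipated rates (device arm, n = 77)**

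- At 1%: 77 × 0.01 = 0.77 expected; P(at least one) = 1 − 0.99^77 = 53.9%.
- At 0.1%: 77 × 0.001 = 0.077 expected; P(at least one) = 1 − 0.999^77 = 7.4%.

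These are upper values, because the protocol gives the rates as ceilings. With fewer than one event expected per listed line, a single attribution decision can be the difference between a signal and none.

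**4. Illustration of distortion**

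The protocol gives neither a background rate for these symptoms nor the share attributed to chemotherapy; both are assumed here. The device excess is set at the protocol's ceiling of 1 point. Cells are expected counts, device v control, 77 per arm.

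| Assumed background | All events recorded | All attributed to chemotherapy | Half kept in device arm, none in control |
|---|---|---|---|
| 10% | 8.5 v 7.7 | 0 v 0 | 4.2 v 0 |
| 20% | 16.2 v 15.4 | 0 v 0 | 8.1 v 0 |
| 40% | 31.6 v 30.8 | 0 v 0 | 15.8 v 0 |

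The first count is 77 × (background + 0.01) and the second is 77 × background; the last column halves the first and sets the second to zero. The same true excess can thus appear as nothing or as an apparent difference of 5.5, 10.5 or 20.5 points.

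**5. What full recording could show**

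For a 1-point excess, SE = √[(p₁(1−p₁) + p₂(1−p₂))/77].

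- 11% v 10%: SE 0.049, 95% CI half-width 9.7 points, power 5.5%.
- 21% v 20%: SE 0.065, half-width 12.8 points, power 5.3%.
- 41% v 40%: SE 0.079, half-width 15.5 points, power 5.2%.

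Power (normal approximation, two-sided 5%) is close to the false-positive rate. Recording every such event removes the attribution bias; it does not make the trial able to detect an excess of this size.

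**The case against.** The best defence is that the Section 25(1) wording is a labelling matter. It refers to the Clinical Trials Act, and Sections 5(4) and 8 name illnesses alongside adverse events, which suggests that wider collection was intended. Ambiguous events also have a way in: the exclusions are worded for effects of anticancer therapy itself, or directly caused by chemotherapy, and Section 25(5) counts as related whatever cannot be excluded. Leaving out background chemotherapy toxicity for a device that already has approval is partly a choice about burden. All this has weight and argues against a full all-cause rewrite. It does not remove the exclusion in Section 5(4) and note f, and it does not say which rule wins when both apply.

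A reader might infer more than the documents support:

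- **That the not-related class is impossible.** It is not. Section 25(1) concerns suspicion of a link to study conduct; Section 25(5) asks about the device and study procedures after assessment. An event suspected at entry may be judged unrelated later. The fit is poor, not contradictory in logic.
- **That the arms are filtered by different written rules.** The chemotherapy exclusion is worded alike for both. What controls lack is assessment of causality to a device they do not have in that period. Differential attribution is a risk of the open-label judgement, not a written asymmetry.
- **That the plan promises event tables by arm.** Section 8, Safety Evaluation, specifies tables by System Organ Class and Preferred Term, but states a split by group only for laboratory tests.
- **That controls lose follow-up.** Section 14(5) says "Participants who have received the investigational device will continue safety follow-up observations" after discontinuation, but Section 25(6) follows all adverse events to resolution or stabilisation (or until the investigator judges further follow-up unnecessary), without an arm limit, and the schedule has a discontinuation assessment.

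**Conclusion.** The point stands in a limited form. The definition in Section 25(1) does not sit well with Sections 5(4) and 25(5), and the chemotherapy exclusion lets an unblinded judgement decide whether abdominal pain, diarrhea and taste disturbance enter the record. This can bias the randomised comparison of those symptoms in either direction.

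A reader might conclude that the arms cannot be compared on safety at all. That goes too far: laboratory tests are summarised by group and do not depend on attribution, and malfunctions such as detachment or swallowing are unlikely to be ascribed to chemotherapy. Efficacy is untouched.

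The size is at most 0.77 expected events per listed line in 77 participants at the 1% ceiling, with a 53.9% chance of seeing any. The distortions in the table rest on assumed background rates and attribution shares and show direction only. The gain from a correction is an unfiltered record, not power. The correction is worth making because it is cheap and the comparative period cannot be repeated.

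**What to change.** 1. Reconcile Sections 25(1), 5(4), note f and 25(5), so that one definition governs recording and the text says what happens when an event could be due to either chemotherapy or the device.
2. Record at least the symptom terms of Section 25(7) (abdominal pain, diarrhea, taste disturbance) in both arms from Day 1, whatever cause is attributed. The exclusion may stay for other chemotherapy toxicity if burden is the concern.
3. Keep causality as a recorded attribute, and use the suspected-related definition only as the reporting trigger.
4. Tabulate these terms by arm for the comparative period regardless of causality, with confidence intervals, and state that the trial is not sized to detect an excess of about 1 point.

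The cost is protocol wording and a few more eCRF entries. No added visits are needed, and the sample size does not change.
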